##### Psychosocial Outcomes

The primary psychosocial outcome is anxiety, as measured by the State Trait Anxiety Inventory (STAI) [45]. The STAI is administered from T1–T4 (see Table 3) to enable analysis within and across time points. Other psychosocial outcomes to be investigated include RGCS knowledge, decisional conflict and decision regret. *A priori* confounders (e.g., the highest level of education attained) and covariates associated with the outcome at *p* < 0.1 in univariable analyses will be included in multivariable analyses. These will take the form of logistic regression modeling for binary outcomes. As these will be planned analyses, probability values of <0.05 will be considered statistically significant. To account for missing data, response bias will be assessed using between-group comparisons of responders and non-responders at different time points. Inverse probability weights from propensity scores will then be generated.

##### Implementation Science

The implementation science research team is using implementation science and behavior change theories, e.g., the Consolidated Framework for Implementation Research [66] and Theoretical Domains Framework [67], to understand the effectiveness of the implemented RGCS program. Barriers were identified earlier in the implementation phase of the study and implementation interventions were developed to overcome these (to be reported separately). A subset of these strategies has been evaluated, with input from the study genetic counselors, for acceptability and feasibility. Enablers that contributed to the successful implementation and effectiveness of rHCP education are also being investigated.

##### Health Economic Analysis

A cost-effectiveness analysis will be conducted taking the costs to the healthcare system as the perspective. A decision tree model with probabilities based on outcomes from MM, costs from the Medicare Benefits Schedule and Pharmaceutical Benefits Schedule, and published data on lifetime costs of disease will be developed. Costs to the health system include the costs associated with IVF decisions, termination of pregnancy, and the expected future healthcare costs of maintaining a live birth with a severe inherited genetic condition. All costs will be standardized to 2022 values. The AQoL-4D will be scored using the Australian values [47] for both parents to identify any changes in quality of life over the 12 months of follow-up. A hypothetical comparator will be used to estimate costs and outcomes for the counterfactual of ‘usual care in the absence of the MM program’. This counterfactual will assign quality of life weights to both parents using population norms [68]; for those parents who have a live birth of a child with a genetic condition, a lower quality of life weight identified from MM and the literature will be assigned for the duration of the expected survival of the child. A quality of life weight for the child with a genetic condition will also be assigned for their expected survival. Quality of life and survival will be combined into quality-adjusted life years (QALYs). All future expected costs and QALYs will be converted into today’s values, discounted using a 5% rate based on Australian policy requirements, as stipulated by MSAC [65]. The difference in QALYs and costs for the MM participants and the counterfactual will be calculated and reported as an incremental cost-effectiveness ratio. TreeAge Pro (2018) will be used in this analysis.

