Research demonstrates there is interest in and support for RGCS, provided it is optional and those offered screening are given sufficient time and information to consider their decision [9,12,13,14,15]. Research has shown increased chance couples may initially express shock and anxiety [16], however, over time report feeling empowered by the information and the ability to make value-congruent reproductive choices [17,18]. These findings highlight the importance of providing RGCS within a model that incorporates informed decision-making with high-quality pre-test information and the provision of appropriate genetic counseling support [18,19].

Internationally, there is substantial variation in access to RGCS, as well as differences in the number and type of conditions screened, how results are returned and managed, if the reproductive couple is screened sequentially or simultaneously, and whether government-funded RGCS is available [1,2]. In Australia, RGCS is currently available largely on a user-pays basis, through commercial entities. However, the Australian Federal Government’s Department of Health recently announced a plan for government-funded carrier screening for three conditions (cystic fibrosis, spinal muscular atrophy and fragile X syndrome) to be implemented in late 2023. 

RGCS is usually ordered through healthcare providers, such as general practitioners, obstetricians, midwives, fertility specialists and genetic health professionals. Barriers to RGCS, including test costs and a lack of awareness amongst healthcare providers and the general community, mean that most increased chance couples are not given the opportunity to learn this information prior to the birth of an affected child [20]. Currently, most people who access RGCS do so in early pregnancy, despite this information being most useful prior to conception [20]. Those accessing RGCS also tend to live in metropolitan areas and utilize private healthcare [20,21,22]. Given this inequality in access, a population-based screening approach would enable RGCS to be made more widely available. 

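### Parental utility comes from participants in one arm and from population norms in the other, so any baseline gap between them is counted as a programme effect in the ICER

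*Protocol article*

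**What the plan says.** The point concerns the Health Economic Analysis paragraph in section 2.7.1 of the protocol article.

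- **Programme arm.** "The AQoL-4D will be scored using the Australian values [47] for both parents to identify any changes in quality of life over the 12 months". Table 3 places the AQoL-4D at T1 (enrolment, before any result), T3 (3 months post result) and T4 (12 months post result).
- **Comparator.** There is no concurrent control: "A hypothetical comparator will be used to estimate costs and outcomes for the counterfactual". This counterfactual stands for usual care without the programme.
- **Comparator utilities.** "This counterfactual will assign quality of life weights to both parents using population norms". For parents who have an affected child, "a lower quality of life weight identified from MM and the literature will be assigned for the duration of the expected survival of the child". The affected child also receives a weight over expected survival.
- **Effect estimate.** "The difference in QALYs and costs for the MM participants and the counterfactual will be calculated and reported as an incremental cost-effectiveness ratio". Future values are "discounted using a 5% rate based on Australian policy requirements".

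The paragraph does not state that the norms are matched to participants on age, sex, pregnancy status or socioeconomic position. It does not name the T1 value as the counterfactual level.

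**The concern.** A QALY difference between two arms is interpretable only if the arms would show the same utility in the absence of the programme. Here one arm is made up of adult couples who are planning a pregnancy or in early pregnancy and who agreed to take part. The other arm carries an external population average. Any difference between those two groups before screening is carried into the numerator of the QALY comparison. It is a bias rather than noise, so a larger sample does not reduce it.

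The imbalance in reach makes this more than a technicality. A change in reproductive outcome is possible only for couples with an increased chance result, put at 1–2% in the Background. A baseline offset applies to two parents in every couple. A utility difference too small to notice in a descriptive table could therefore rival the effect being estimated. Sections 2.7 and 3 say that the study's results inform an application for public funding, so the ratio may carry weight.

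**Working it through.** The article states no QALY difference, ICER, norm value or participant utility, so there is no figure to reproduce. What follows is a sensitivity calculation.

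**Inputs from the article:** 8350 couples (revised target, section 2.4); 1–2% increased chance couples (Background); 5% discount rate (Health Economic Analysis).

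**Assumptions:** participant-minus-norm gap of 0.005 to 0.02 per parent, lasting one year; one pregnancy per increased chance couple; 1 in 4 affected; all affected births averted; parental decrement of 0.05 to 0.1 each for 20 years.

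**Step 1: QALYs created by the gap alone.** Gap × 2 parents × 8350 couples × 1 year.
- 0.005 × 2 × 8350 = 83.5
- 0.01 × 2 × 8350 = 167
- 0.02 × 2 × 8350 = 334

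A negative gap gives the same figures with a minus sign.

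**Step 2: real parental gain.** Couples × share at increased chance × 0.25 × 2 parents × decrement × annuity, where the annuity is (1 − 1.05^−20) / 0.05 = 12.46.
- Upper: 8350 × 0.02 × 0.25 = 41.75 births; 41.75 × 2 × 0.1 × 12.46 = 104
- Lower: 8350 × 0.01 × 0.25 = 20.9 births; 20.9 × 2 × 0.05 × 12.46 = 26

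**Step 3: break-even gap.** Gain / (2 × 8350).
- 26 / 16,700 = 0.0016
- 104 / 16,700 = 0.006

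The number of couples cancels in this ratio, so the break-even does not depend on the recruitment target being met.

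**Step 4: wider grid.** With 50% or 90% of affected births averted, decrements of 0.05 to 0.20 and durations of 5 to 20 years, the real parental gain is 0.0005 to 0.022 QALY per couple (median about 0.004). The one-year break-even gap is then 0.0003 to 0.011 (median about 0.002). Gaps of 0.01, 0.02 and 0.05 add 0.02, 0.04 and 0.10 QALY per couple, which is 0.9 to 185 times the parental gain.

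**Step 5: child QALYs.** The model also gives the affected child a weight. If each averted case is credited with an assumed 5 to 18 child QALYs, this adds 0.006 to 0.081 QALY per couple. For example, 0.02 × 0.25 × 0.9 × 18 = 0.081. A one-year gap of 0.01 (0.02 per couple) is then not always larger than the real effect.

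**Step 6: common baseline.** If both arms start from the same parental value, the gap is subtracted from itself and the artefact is 0. Measured change and event-related decrements remain.

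**The case against.** The strongest reply is that the article never says measured levels populate the programme arm. It says the AQoL-4D serves to identify changes over 12 months. A model that adds those changes to a baseline shared by both arms would also fit that sentence, and the offset would cancel. T1 is the only pre-result measurement, so it is probably already used to compute the change. This stands in part: the use of levels is implied, not explicit. But QALYs require levels in both arms, and norms are assigned only to the counterfactual. If a shared baseline is intended, the paragraph does not convey it.

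A second reply is that the design limits selection. Section 2.5.2 sets targets by region and by public or private care, section 2.6.1 restricts recruitment once regional targets are met, and representativeness is assessed under Quantitative Analysis. These measures may narrow the gap, but they balance geography and care setting rather than utility, and the representativeness check is descriptive. The inverse probability weights under Psychosocial Outcomes address survey non-response, not the difference from norms.

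A reader might go further and infer that healthier or better-off volunteers inflate the programme's benefit beyond its real size. The documents do not support that. The Background remark that "Those accessing RGCS also tend to live in metropolitan areas and utilize private healthcare" describes existing, largely user-pays screening, which this free programme was designed to broaden, and it says nothing about utility. Section 2.5.2 also admits couples who already know of a genetic risk, and some participants are in early pregnancy; either could shrink or reverse the gap. Nor do the parental QALYs in the working represent the whole gain, since child QALYs are modelled too.

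It is also fair that the content of the norms and any planned sensitivity analyses may be set out in a fuller document. Their absence from the article is not the point. The point is the stated rule that gives norms to one arm only.

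**Conclusion.** The concern holds in a limited form. As written, the economic analysis takes parental utility from participants in one arm (by implication) and from population norms in the other (explicitly), and reports the difference as an ICER. Any baseline difference between the two sources is then attributed to the programme, and no safeguard stated in the article removes it.

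The direction of the bias is unknown and its actual size cannot be derived from the article. What can be said is that the comparison is fragile: under the stated assumptions, a one-year gap of only about 0.0016 to 0.006 per parent equals the whole parental gain. An assumed gap of 0.005 is already within or above the 26 to 104 QALY range, and 0.02 exceeds it. Crediting child QALYs weakens this, so the artefact should be described as possibly as large as the real parental effect, not as larger than the real effect overall. The gap, decrement, duration, averted share and 1-in-4 risk are all assumptions.

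**What to change.** State in the Health Economic Analysis that both arms use one parental baseline:

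- Set the counterfactual parental level to participants' own T1 AQoL-4D, measured before any result.
- Take the programme effect as change from T1, plus the event-related decrements already planned for parents of an affected child.
- Keep population norms only as a sensitivity analysis, or for years beyond follow-up, and apply them identically in both arms.

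This changes model inputs only. Section 2.6.3 has all participants complete the T1 questions whether or not they choose screening, so no new data collection is needed. The downside is small: T1 follows the offer, so it may partly reflect the offer itself or early pregnancy. The sensitivity analysis with common norms in both arms would show whether that matters.

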##### Qualitative Analysis

Interviews will be transcribed with participants assigned a pseudonym or participant code. Data will be co-coded and managed using NVivo (QSR International). Thematic analysis, or content analysis as appropriate, will be used for the analysis of qualitative interview data. Data gathered from rHCPs and the MM study team will be analyzed using appropriate implementation science and behavior change frameworks.

#### 2.7.2. Use and Analysis of Genomic Data

When providing consent to RGCS as part of the study, participants are also asked to provide consent to share their de-identified genomic data to advance the scientific knowledge of genetic conditions. Genomic data generated by the study are stored by the three laboratories as required by the Australian regulatory body, the National Pathology Accreditation Advisory Council (NPAAC). Additionally, the data are stored in a re-identifiable format, in a secure central data repository managed by Australian Genomics. Through a data access request process, de-identified genomic data can be shared with other ethically approved research studies and with genomic databases, in accordance with a participant’s data sharing preferences. The project is currently working with collaborators to generate harmonized summary data regarding allele frequencies which can be made openly available to researchers and diagnostic laboratories. Summarized data regarding allele frequencies will also be made available to researchers and diagnostic laboratories via the Centre for Population Genomics.

## 3. Discussion

This study is the first of its kind to investigate the acceptability and feasibility of a government-funded RGCS program screening over 1000 genes. The rationale behind the Australian Federal Government’s funding of the MM research study is to investigate how best to deliver a potential, future, publicly funded, easily accessible RGCS program. A strength of the study design is the ability to capture attitudes and experiences across various time points, including at the offer of screening and post result. The study will provide important data to inform decisions about the implementation of an ethically robust national RGCS program and inform the development of models for delivering carrier screening services. Findings will also be presented in scientific publications, at national and international conferences, disseminated to participants, and a summary will be available on the study website [23]. To support the translation of study findings into health services policy and clinical practice, an application has been prepared and submitted to the MSAC. The aim of the application is to request government funding of RGCS for a widely accessible and comprehensive screening program. In addition, the study findings will inform the preparation and submission of recommendations regarding the implementation of a population-wide RGCS program to both Federal Australian and State/Territory Governments, and professional bodies including RANZCOG, RACGP, RCPA and HGSA.

## Figures and Tables

**Figure 1 jpm-12-01781-f001:**
[figure not shown]
Mackenzie’s Mission’s governance structure.

**Figure 3 jpm-12-01781-f003:**
[figure not shown]
Data collection timepoints for people offered reproductive genetic carrier screening in the Mackenzie’s Mission study.

**Figure 4 jpm-12-01781-f004:**
[figure not shown]
Laboratory testing and management of results in the Mackenzie’s Mission study.

**Table 1 jpm-12-01781-t001:** Inclusion and exclusion criteria.

Inclusion Criteria	Exclusion Criteria
Planning to become pregnant or in early pregnancy (9 weeks and 6 days of gestation or less ^a^)	Pregnant and 10 weeks of gestation or greater ^a^
Both members of the reproductive couple are available to participate in the study and provide a sample for testing	Only one member of the reproductive couple agrees to participate in the study Both members of the reproductive couple are not available to be tested at the same time
If a donor(s) is being used for the pregnancy, the donor(s) must be available to provide a sample for testing and consent to having RGCS	A donor(s) is being used for the pregnancy and the donor(s) is/are not available for testing, or an anonymous donor is being used A donor(s) is being used for the pregnancy and not all people involved in the pregnancy agree to participate in the study
Both members of the reproductive couple are aged 18 years or over	One or both members of the reproductive couple are less than 18 years old

^a^ To ensure results are returned in an appropriate timeframe, gestation cut-offs for each state/territory were established for cases where screening had occurred in early pregnancy. The gestation cut-off for enrollment in MM and undergoing RGCS has changed throughout the course of the study. When participant recruitment first commenced, only non-pregnant couples were eligible to enroll in the study. As the study progressed, recruitment numbers and test turnaround times at the three laboratories providing the RGCS were carefully monitored. The recruitment of couples in early pregnancy began when test turnaround times had become sufficiently fast enough to be able to return results in an ethically and clinical acceptable timeframe. Impacts of the SARS-CoV-2 pandemic, workplace restrictions and postage considerations also required reassessment of gestation cut-offs at various points during the study. For simplicity, we refer to a gestation cut-off of less than 10 weeks at enrollment and less than 11 weeks at sample receipt by the laboratory, as these have been the latest possible gestation cut-offs utilized and evaluated during the study.

**Table 2 jpm-12-01781-t002:** Data collection tools for recruiting HCPs in the Mackenzie’s Mission study ^a^.

Timepoint	Data Collection Tool(s)	Main Focus of Data Collection
Prior to education to become an rHCP	HCP survey 2	Potential barriers to implementing RGCS Factors that might influence confidence/ability to refer people for RGCS Readiness to change practice Knowledge of concepts relating to RGCS
Eight to 12 weeks after rHCP education	HCP survey 3 HCP interview guide ^b^	Knowledge of concepts relating to RGCS and study processes Attitudes toward RGCS and factors influencing recruitment, such as knowledge, ability and confidence Views on factors that may influence patient accessibility to RGCS, including socioeconomic status, geographic location, language, cultural background, health literacy and disability Reasons for offering/not offering the study to patients and the reasons patients provide when they decline to take part
Toward the end of the study	HCP survey 4	Rating identified facilitators to offering RGCS

^a^ HCP survey 1 is not included in this table as it was administered to HCPs prior to their involvement in MM. ^b^ Interviews are being conducted by telephone or video conference, and audio-recorded.

## Data Availability

Study data collection tools, education modules and consent content are available from the corresponding author upon reasonable request.
